### Blinding

The trial manager (SA) assessing outcome measures at baseline, 8 weeks and 3 months follow-up will be blinded to group allocation and will not be involved in randomisation or intervention delivery.

### Randomisation and concealed allocation

The randomisation schedule will be generated using a computer-generated random sequence in advance of trial commencement by the trial statistician (KB), who will not be involved in recruitment or outcome assessment. Randomisation will be stratified by recruitment method (GP, secondary care or community/social media). Participants will be randomly allocated (1:1 ratio) using random blocks of size 2, 4, 6, or 8 within each stratum. Within the intervention arm (n=32) a further 1:1 blocked randomisation (block size 2, 4 or 6) will be developed for random allocation of the EDX-Ireland group, within the SWAT, to either the smartphone application (n=16) or paper-based diaries (n=16). Randomisation and allocation will be done by the PI ([name]), who will not be involved in screening or baseline assessment of trial participants, thus maintaining concealed allocation.

### Interventions

The EDX intervention is described based on the Template for Intervention Description and Replication (TIDieR) (
Hoffmann *et al.*, 2014).

The EDX-Ireland intervention will be delivered in four physiotherapy clinics located in different geographical areas in Dublin. Physiotherapists will have attended a training session outlining study objectives and requirements, demonstrating the detailed education material, the theoretical and practical part of the exercise protocol and progressions. Additionally, a detailed study manual will be provided for reference (
Mellor *et al.*, 2016).

The EDX-Ireland intervention will involve six face-to-face sessions with a physiotherapist, delivered over eight weeks (60 mins for the initial session and 30 mins thereafter). The sessions will be scheduled as weekly appointments for the first four weeks and the final two sessions will be delivered at fortnightly intervals. Participants will receive education on tendon care and gradual progression of tendon loading. This will be delivered via an 18-minute video, which was used in the LEAP trial (provided via DVD), which will be provided to study participants via the online Physiapp patient-facing companion application, used alongside the Physitrack online exercise prescription platform (
https://www.physitrack.com/). The education video explains relevant basic anatomy, terminology related to tendinopathy and bursitis, risk factors, and advice related to sitting, lying positions walking and load modification. Participants will be asked to watch the education video prior to their first appointment with the physiotherapist. Education will also be reinforced by the physiotherapist over the 8-week intervention period. The treating physiotherapist will also provide graduated exercise with 4-6 exercises performed six days a week, with alternate low and high load days, and one rest day. The exercise programme includes three key streams:

1. Isometric abduction: low load isometric abduction training in supine and standing, to improve muscle coordination and control, and to potentially assist with pain relief.

2. Functional loading: bridging (double-leg, offset and single-leg exercises) and squatting (double-leg, offset, single-leg stance and squat, step-ups) progressions with an emphasis on gluteal muscle recruitment and femoropelvic control.

3. Abductor loading: targeted frontal plane abductor muscle and tendon loading to improve load tolerance by applying progressively higher loads across the abductor muscles, as tolerated. This includes sidestepping tasks and standing band-resisted hip abduction.

Week 1 will focus on familiarisation with the basic program and load management strategies. Week 2 will involve early loading and optimisation of movement patterns in the base exercises. Weeks 3-8 focus on graduated loading, where participants will perform exercises, six days a week, with three of those days including exercises performed at a 'hard' to 'very hard' level. These hard days will alternate with three ‘light’ days’ and one rest day. The physiotherapist will monitor exercise difficulty level, exercise technique and pain response to exercise. Level of exercise difficulty will be monitored with the Borg Scale of Perceived Exertion (6-20 scale), where isometric abduction will be performed at a 'light' level (Borg 11-12), functional loading at a 'somewhat hard' to 'hard' level (13-15), and targeted abductor loading from 'somewhat hard' towards 'hard' to 'very hard' level (14-17), depending on response to loading. A maximum of 5/10 on a pain NRS will be allowed as long as it does not result in increased pain that night or the next day. Other everyday activity loading that participants are undertaking, along with the exercise programme and technique, will be reviewed and modified accordingly to reduce loading levels. Key differences between the exercise programme used in the LEAP and LEAP-Ireland trial include the number of in-clinic days per week and number of weeks of treatment. Additionally, the LEAP-Ireland trial will not entail use of a sliding platform with spring resistance during weeks 3-8; resistive exercise bands will be used to provide resistance. Details of the exercise programme with images, used in the LEAP trial are available in Supplemental Table 2 of the LEAP trial (
Mellor *et al.*, 2018).

### Study Within A trial (SWAT)

To test objective 7, the 32 participants randomly allocated to the EDX-Ireland intervention will also be randomly allocated to either a ‘PhysiApp’ or ‘Diary’ group for recording of home exercises, using a second computer-generated random sequence, prepared by the trial statistician. Participants will be informed at the time of group allocation by the randomiser ([name]). Treating therapists will be provided with access to Physitrack (Physitrack Ltd, London, UK), an online exercise management system used by physiotherapists for exercise prescription for the duration of the recruitment and intervention period. Both groups (‘PhysiApp’ and ‘Diary’) will use the patient-facing companion app, PhysiApp (Physitrack Ltd, London, UK), for home exercises, but only the ‘PhysiApp’ group will record exercise adherence on the app. Those assigned to the ‘Diary’ group will be provided with a paper-based diary to record exercise completion and the exercise recording function in PhysiApp will be deactivated. Physiotherapists will check adherence at each appointment and assist with any barriers to exercise completion.

### Usual care

In the LEAP trial '’wait and see’’ arm, participants attended one 30-minute session with a trial physiotherapist, where they received reassurance that the condition is likely to resolve over time, as well as advice regarding general tendon care and self-management (
Mellor *et al.*, 2016). However, usual care in the LEAP-Ireland trial was chosen as the comparator for this study to determine if it is an appropriate comparator, and to identify the exact constituents of usual care, in advance of conducting a full-scale RCT. Usual care for this trial is defined as the treatment that a participant has followed so far or has been prescribed by their referrer into the trial (
*i.e.*, GP, orthopaedic consultant, rheumatologist or musculoskeletal triage physiotherapist). For those not referred from a healthcare practitioner (
*e.g.*, community recruitment/social media), usual care may not be relevant, but any healthcare utilisation will be recorded on a pre-standardised form. Participants randomised to the Usual Care group will receive an information leaflet only with general advice to remain active within limits of pain, and reassurance that the condition will improve with time. The information leaflet is identical to that used in the LEAP Trial, however, no one-off education physiotherapy session will be provided for the Usual Care group. 

### Intervention acceptability

To further explore trial feasibility and acceptability (objectives 8 and 9), semi-structured interviews will be conducted with approximately 18 participants (nine from both groups) to explore their experiences of the trial, intervention content, face-to-face clinic interaction, HEP completion, and acceptability of the smartphone app or paper diaries for HEP recording. The topic guides will be developed using the Theoretical Framework of Acceptability (
Sekhon *et al.*, 2017). Semi-structured interviews will also be conducted with treating therapists (n=7) to ascertain their perspectives of the acceptability of the EDX-Ireland intervention. Interviews will also be undertaken with approximately 8-10 healthcare professionals (doctors or musculoskeletal triage physiotherapists) who referred participants into the trial and were allocated to usual care, to explore their knowledge of management options for gluteal tendinopathy, their rationale for choice of usual care, as well as any barriers or facilitators to providing optimal care for gluteal tendinopathy. Interviews will be audio recorded and transcribed verbatim for thematic analysis.

### Outcomes measures

**
*Primary outcome measures.*
** Primary outcomes focus on feasibility issues including success of recruitment and retention to the 3-month time point. Details of feasibility outcomes and methods used to collect these outcomes are outlined in
Table 3.

**Table 3. T3:** Feasibility outcomes.

Objective	Data collection method
To assess recruitment rates and determine the success of different patient recruitment methods community recruitment, primary care and secondary care) To assess short (8-week) and medium-term (3-month) retention rates	• Number of individuals who contact the research team about the trial (community recruitment) • Recruitment source of each person who undergoes screening process • Number who do/do not consent to telephone screening • Number who are eligible/ineligible to proceed to physical screening • Number who are eligible/ineligible to proceed to MRI • Number who are eligible/ineligible based on MRI findings • Number who are eligible based on MRI findings but decline to participate • Number who consent to participate in the study • Number randomised to participate in the study • Number who attend for 8-week and 3-monthfollow-up • Number who cannot be contacted • Number who do not attend • Number who cannot attend/cancel follow-up (reasons)
To identify the constituents of ‘usual care’ and to determine if inclusion of a usual care arm is feasible and appropriate without the potential for co- intervention bias	Referral sources will be asked to complete a checklist of usual care options (including medications, referral for physiotherapy/other healthcare services). This will be cross-referenced against the participant-completed health and cost questionnaire. Participants will also complete details on current and past treatment for gluteal tendinopathy at baseline assessment.
To estimate the effect size for a likely primary study outcome in a future definitive trial	Based on clinical outcomes collected at 8 weeks and 3 months
To determine outcome measure completion	Completion rate of clinical outcomes collected at baseline, 8 weeks and 3 months
To assess the feasibility of collecting healthcare utilisation and cost data for future cost-effectiveness analysis in a definitive trial	Participants will complete questionnaires on use of pain medications, visits to GP and other medical specialties, investigations, attendance at physiotherapy or other healthcare practitioners or, hospital attendance for their hip pain until the 3-month follow-up
To assess if adherence to the home exercise programme of those allocated to EDX-Ireland differs when recorded on a smartphone application compared with paper diaries	Adherence to the home exercise programme will be recorded by the study participant using the smartphone app or paper-based diary
To assess participants’ and therapists’ acceptability of a smartphone-based application (app) for recording home exercise Adherence in the EDX arm To assess the acceptability of the EDX intervention and usual care from the perspective of study participants and service providers (treating therapists and providers of usual care)	Semi-structured interviews of study participants to explore acceptability of the paper diaries and smartphone app for exercise provision and adherence recording

MRI, Magnetic Resonance Imaging; EDX, EDucation and eXercise.

**
*Secondary clinical outcomes.*
** The following secondary outcomes, which are aligned to core domains recommended for use in tendinopathy research (
Vicenzino *et al.*, 2019) will be assessed at baseline, 8 weeks and 3 months.

*The Global Rating of Change (GROC)* is a 15-point rating scale, completed by the patient based on their perceived overall change in their hip condition and ranges from –7 (a very great deal worse) to +7 (a very great deal better) (
Kamper *et al.*, 2009) and allows patients to consider factors that they consider important for their clinical situation.

Pain severity will be measured using a 11-point
*Numerical Pain Rating scale (NPRS)* under two conditions of pain; on activity/loading and pain in the last week. It is reliable, valid and easy to administer. A minimal important difference (MID) of 1.5 points or 15% has been ascertained for musculoskeletal pain (
Abbott & Schmitt, 2014).

*Victorian Institute of Sport Assessment-Gluteal (VISA-G)* is a self-reported questionnaire, which measures disability associated with gluteal tendinopathy. It contains eight items, rated on an 11-point scale, related to pain and function and is reliable and valid (
Fearon *et al.*, 2015).

*The Patient-Specific Functional Scale (PSFS)* is a self-reported, patient-specific measure, designed to assess functional change. It is reliable and valid across various musculoskeletal disorders (
Abbott & Schmitt, 2014).

Psychological distress, which is associated with gluteal tendinopathy (
Plinsinga *et al.*, 2018;
Plinsinga *et al.,* 2020) will be evaluated using two measures. The
*Pain Catastrophising Scale (PCS)* is a valid and reliable 13-item self-report measure, which asks about thoughts and feelings associated with pain (
Sullivan *et al.*, 1995). The
*Patient Health Questionnaire (PHQ)* is a valid and reliable self-reported questionnaire for measurement of depressive symptoms. It contains nine questions with a score range of 0-27. A score of ≥5 indicates mild depressive symptoms, ≥10 moderate, ≥15 moderately severe and ≥20 severe (
Kroenke *et al.*, 2001).

The
*Pain Self-Efficacy Questionnaire (PSEQ)* assesses people’s confidence in performing activities when they are in pain (
Nicholas, 2007). It contains 10 items answered on a 7-point Likert scale.

*The EQ-5D-5L* is a generic measure of health-related quality of life (HR-QOL). Each health state is ranked and transformed into a single index score, called the utility score. This utility score will be used to express the Quality-Adjusted Life Years (QALY), which is commonly used in analyses of cost-effectiveness (
Rabin & de Charro, 2001).

*The Central Sensitisation Inventory (CSI)* is a 25-question self-reported screening instrument designed to identify presence of centrally-mediated pain sensitisation (
Mayer *et al.*, 2012). A cut-off score of ‘40’ of ‘100’ yielded good (81%) sensitivity (
Neblett *et al.*, 2015).

*Isometric Hip Abductor Muscle Strength* will be tested in supine using a hand-held dynamometer (MicroFET
^®^2 Digital Handheld Dynamometer (Hoggan Scientific, Utah, USA). The leg will be positioned to minimise compression of the gluteal tendons against the greater trochanter. A non-elastic fixation belt will be placed around the patient’s pelvis and secured to the bed to minimise any trunk/pelvic movement during testing (
Allison *et al.*, 2016b). Pain severity using a 0-10 NPRS will be assessed immediately before and during strength testing to ascertain the impact pain may have on maximal effort.

Healthcare use and costs will be measured using a modified version of the
*Osteoarthritis Cost and Consequences Questionnaire (OCC-Q)* (
Pinto *et al.,* 2011) as was used in LEAP Trial (
Mellor *et al.*, 2018;
Wilson *et al.*, 2023). Modifications included replacement of the wording ‘osteoarthritis’ with ‘hip pain’. Questions related to impact on work and previous joint replacement were removed..

All assessments will take place at RCSI. Participants will complete PROs using Research Data Capture (REDcap) online electronic data capture tool (
Harris *et al.*, 2019), hosted at RCSI, for the baseline, 8-week and 3-month follow-up.

### Adverse events

Adverse events related to the EDX intervention are considered low risk in this trial. Treating physiotherapists will record and report adverse effects to the Principal Investigator. All adverse events will also be reported to the Trial Management Group (TMG) and the Trial Steering Committee (TSC). Serious adverse events will be reported to the trial sponsor and may result in trial withdrawal.

### Participant confidentiality and data management

Participants will be identified by a study-specific unique identifier number (UIN) during the study. Processing of any personal data will comply with national and EU General Data Protection Regulations (GDPR), and compliance with GDPR will be maintained throughout the trial (
European Commission, 2018).

### Statistical analysis

Descriptive analysis will include proportions and 95% confidence intervals (CI), means and standard deviations (SD) or medians and inter-quartile ranges (IQR) where appropriate. Feasibility outcomes of recruitment and retention rates will be descriptively reported overall across both arms of the trial (percentages and 95% CIs) and by method of recruitment. Outcome measure completion will be described both by participant and by outcome measure using percentages. Recruitment rates will be calculated as the number of participants who consent to participate divided by the number of eligible participants approached. Trial retention rates will be calculated from the number of participants who complete all outcome measures divided by the number who record baseline outcome measures. Adherence rate of exercises within the SWAT for the EDX group, and types of usual care for the control group will be reported as percentages.

Results of secondary clinical outcomes including NPRS, hip abduction strength and measures of psychological distress will be reported using means and SD or medians and IQR, where appropriate for baseline, 8- and 3- month follow-up. Statistical analysis will be performed using Stata v18 (StataCorp, College Station, Texas, USA).

Sensitivity analysis will be conducted as a secondary analysis to impute any missing data using multiple imputation. The resource use data captured by the OCC-Q will be valued using unit costs derived from local and national sources and will be analysed in a manner consistent with the clinical outcome data.

Qualitative data from interviews will be transcribed verbatim. A two-stage analysis will be undertaken, initially through inductive line-by-line coding of the extracted results to identify emergent themes, followed by deductive mapping of pre-identified codes to the Theoretical Framework of Acceptability (
Sekhon *et al.*, 2017).

Trustworthiness will be attained through procedures such as member checking, maintaining a reflexive journal of the research procedures and a clear audit trail of the process (
Braun & Clarke, 2014).

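### Retention is defined in the analysis section as completing all outcome measures at an unnamed visit, whereas Table 3 measures it by attendance at 8 weeks and 3 months; no by-arm rate is stated

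*Protocol article*

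**What the plan says.** The protocol article treats retention in three places.

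- Outcomes measures, primary outcomes: "Primary outcomes focus on feasibility issues including success of recruitment and retention to the 3-month time point".
- Table 3, in the row that covers recruitment and both 8-week and 3-month retention, lists attendance data: "Number who attend for 8-week and 3-monthfollow-up", with counts of people who could not be contacted, did not attend or cancelled. A separate row covers outcome completion: "Completion rate of clinical outcomes collected at baseline, 8 weeks and 3 months". This matches Objective 5, which stands apart from Objective 1 on recruitment and retention.
- Statistical analysis gives the formula: "Trial retention rates will be calculated from the number of participants who complete all outcome measures divided by the number who record baseline outcome measures". On reporting level it says: "Feasibility outcomes of recruitment and retention rates will be descriptively reported overall across both arms of the trial", and also by method of recruitment. Completion is handled in its own sentence: "Outcome measure completion will be described both by participant and by outcome measure using percentages".

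The Sample size section plans on retention of at least 80%, with a 95% CI of 69.8% to 90.2% from 60 participants, and then raises the target to 64 (32 per arm).

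**The concern.** One primary outcome has two definitions. Table 3 counts people who come back; the formula counts people with a full set of measures. The formula therefore merges two things that the article elsewhere keeps apart, and it can only lower the figure relative to attendance. It also does not say whether the full set is needed at 8 weeks, at 3 months or at both, although Table 3 asks for both time points.

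The reporting level adds a second gap. The trial offers one arm six physiotherapy sessions and gives the other an information leaflet, besides whatever care those participants already follow or have been prescribed. Unequal loss is foreseeable with such different contact, and a pooled rate cannot show it.

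At stake is the retention rate carried into the definitive trial (Objective 1). If that rate is understated, the allowance for drop-out is too large. If loss differs by arm, a single pooled allowance misses it.

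**Working it through.** **Inputs from the article.** Planned n = 60 for the interval and 64 in the trial, 32 per arm; planning value 80%. Ten measures per visit: GROC, NPRS, VISA-G, PSFS, Pain Catastrophizing Scale, PHQ, Pain Self-Efficacy Questionnaire, EQ-5D-5L, Central Sensitisation Inventory and hip abductor strength. The modified cost questionnaire makes eleven.

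**Assumed, because the article gives no figure.** Attendance of 90%; each measure missed by 1%, 2% or 5% of attenders.

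**Step 1: the plan's own interval.** Wald limits are p ± 1.96 × √(p(1−p)/n). With p = 0.80 and n = 60: 1.96 × √(0.16/60) = 0.101, giving 69.9% to 90.1%. The stated limits are 69.8% and 90.2%, so the figure reproduces to 0.1 point and is not in dispute. It is a pooled interval.

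**Step 2: effect of requiring all measures.** If misses are independent, retention = attendance × (1 − m)^k. If all misses fall on the same people, it is attendance × (1 − m).

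| Missed per measure (m) | k = 10, independent | Same people |
|---|---|---|
| 1% | 0.90 × 0.99^10 = 81.4% | 0.90 × 0.99 = 89.1% |
| 2% | 0.90 × 0.98^10 = 73.5% | 0.90 × 0.98 = 88.2% |
| 5% | 0.90 × 0.95^10 = 53.9% | 0.90 × 0.95 = 85.5% |

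With eleven measures, 2% missed and independence, the figure is 0.90 × 0.98^11 = 72.1%.

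The unnamed visit also matters. If 90% attend both visits and all ten measures are required at both, 2% missed with independence gives 0.90 × 0.98^20 = 60.1%.

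**Step 3: what this does to a later sample size.** The inflation factor is 1/retention. At 90% it is 1.11; at 73.5% it is 1.36, which is 0.90/0.735 = 1.22 times as many participants. At 88.2% the ratio is 0.90/0.882 = 1.02.

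**Step 4: what the pooled rate can conceal.** 51/64 = 79.7% arises from any of these illustrative splits (difference with Wald 95% CI):

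| Split | Rates | Difference (95% CI), points |
|---|---|---|
| 28/32 v 23/32 | 87.5% v 71.9% | 15.6 (−3.7 to 35.0) |
| 29/32 v 22/32 | 90.6% v 68.8% | 21.9 (2.9 to 40.8) |
| 30/32 v 21/32 | 93.8% v 65.6% | 28.1 (9.7 to 46.6) |

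A nearly even 26/32 v 25/32 gives the same total.

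**Step 5: precision of by-arm figures.** At 80% in one arm of 32: ±1.96 × √(0.16/32) = ±13.9 points, or 66.1% to 93.9%. For the difference at 80% in each arm: ±1.96 × √(2 × 0.16/32) = ±19.6 points.

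**The case against.** Several points on the other side stand.

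- **No decision rule.** A reader might infer that the formula could fail a trial that kept nearly everyone, or that pooling could pass one with a failing arm. The article states no progression criterion. Its feasibility rates are descriptive, and 80% is only the value at which an interval was computed.
- **Clustered misses are plausible.** All assessments take place at one centre and patient-reported outcomes are entered electronically, so gaps may concentrate in a few people. The distortion at 2% missed is then under 2 points. The independent-miss figures are the unfavourable end of a range.
- **Partial cover.** Completion is also reported by participant and by measure, so a reader could see that a low retention figure came from one skipped instrument. This softens the definition problem. It does not help with arms, because no split by arm is stated there either.
- **By-arm rates are not excluded.** The article does not forbid them, and a fuller protocol or analysis plan may supply them. The attendance counts will exist, so unequal loss is recoverable. What stands is that the article fixes a reporting level that leaves out arm.
- **Objective 4 is not about retention.** A reader might link pooling to the question of whether a usual-care arm is feasible. That objective concerns the content of usual care and co-intervention bias, and Table 3 assigns it referrer checklists and participant questionnaires.
- **The denominator is nearly right.** Randomisation follows the baseline assessment, so people with baseline data and people randomised differ only by anyone lost in between.
- **GROC at baseline.** The article lists this change score among the baseline measures, but the denominator needs only recorded baseline measures, so the listing does not alter the retention figure.

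None of this removes the conflict between the formula and Table 3. Leaving it to an analysis plan does not resolve it: a plan that follows the formula inherits the problem, and one that follows Table 3 departs from the published formula.

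**Conclusion.** The point holds as an inconsistency in the definition of a primary feasibility outcome, together with a reporting level that omits arm. The formula understates retention as Table 3 measures it. How far depends on missingness that the article does not give: at an assumed 90% attendance and 2% missed per measure over ten measures, the one-visit figure lies between about 74% and 88%. The larger gap rests on independent misses; under full clustering the effect is small. For the reporting level, a pooled 80% is compatible with between-arm differences from near zero to 28 points in the splits shown, which are illustrations and not predictions. The documents do not support saying that the trial would wrongly pass or fail, or that the planned interval is wrong.

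**What to change.** In Statistical analysis, replace the retention formula with two rates, one at 8 weeks and one at 3 months: the number attending (or the number providing the GROC, which the Sample size section names as the outcome for powering the definitive trial) divided by the number randomised. Choose one numerator and use it in Table 3 as well. Using the number randomised as the denominator is a minor clarification.

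Report each rate by arm with its 95% CI, as well as overall and by recruitment route. If the between-arm difference is given, show its 95% CI and note that it will be imprecise, about ±20 points with 32 per arm. Report the proportion with all measures complete, per visit, under outcome completion (Objective 5).

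The cost is wording only. Table 3 already plans the attendance counts, and allocation is known at analysis, so no new data or change in sample size is needed. It should be settled before the feasibility results are analysed.

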Although current best evidence indicates, based on the LEAP trial findings, that a combination of physiotherapist-delivered exercise and education is clinically and cost-effective for management of GT (
Mellor *et al.*, 2018;
Wilson *et al.*, 2023), there are currently no clinical guidelines to guide practice. Indeed, usual care of gluteal tendinopathy by medical practitioners, to whom patients may initially present, is currently unknown.

This feasibility RCT will contribute to the following gaps in the literature: 1) to examine the feasibility of conducting a future definitive RCT to compare effectiveness of six sessions of physiotherapy-led Education on load management plus eXercise (EDX-Ireland) EDX to usual care and 2) to quantify usual care in GT management in Ireland.

Completion of a daily Home Exercise Programme (HEP) is an integral part of the EDX-Ireland intervention. Traditionally, paper-based diaries are used to record adherence, but adherence can be over-reported compared with electronic diaries (
Stone *et al.,* 2003). An RCT demonstrated improved exercise adherence using an app in people with musculoskeletal conditions, compared to paper handouts (
Lambert *et al.*, 2017), with high satisfaction rates reported by those who used the app. Given that >90% of phone users in Ireland have smartphones (
Deloitte, 2023), the use of app-based technology may be potentially more feasible to monitor and enhance treatment adherence.

We therefore aim to evaluate the feasibility of conducting a future definitive RCT, using a reduced dose (6 sessions) of a proven-effective physiotherapy treatment (14 sessions) consisting of EDucation plus eXercise for GT in an Irish context. A Study Within A Trial (SWAT) will compare smartphone application
*versus* paper-based diary for exercise adherence measurement. A SWAT is a type of research study that has been embedded within a host larger trial to evaluate alternative ways of delivering or organising a particular trial process (
Treweek *et al.*, 2018).

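### The SWAT randomises 16 v 16 to test whether adherence differs between app and diary, but the stated analysis reports only percentages, with no difference or interval

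*Protocol article*

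**What the plan says.** The Objectives list, under number 7, an assessment of whether adherence to the home programme in the EDX-Ireland arm differs between app and paper-diary recording. Table 3 repeats this. The section on the SWAT makes the purpose of the second randomisation explicit: "To test objective 7, the 32 participants randomly allocated to the EDX-Ireland intervention will also be randomly allocated" to app or diary. The section on randomisation and concealed allocation gives the split as 1:1, 16 per group.

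The Statistical analysis section then deals with the result in one clause: the "Adherence rate of exercises within the SWAT for the EDX group", together with types of usual care in the control group, will be reported as percentages. The same paragraph says that recruitment and retention rates will be given as percentages with 95% confidence intervals, overall and by recruitment method, and gives a numerator and denominator for each.

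On frequency, the Background says: "Completion of a daily Home Exercise Programme (HEP) is an integral part of the EDX-Ireland intervention". The Interventions section gives "4-6 exercises performed six days a week, with alternate low and high load days, and one rest day", and later adds: "Weeks 3-8 focus on graduated loading, where participants will perform exercises, six days a week".

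**The concern.** The objective is comparative and the allocation is randomised, but the stated analysis is descriptive and refers to the EDX group as a whole. Read literally, it could be met by one pooled percentage. Read generously, it yields one percentage per SWAT arm. Neither reading gives an estimate of the difference with its uncertainty, which is what the objective calls for.

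At stake is the use made of the SWAT result. Two bare percentages from groups of 16 invite over-reading. A gap of 10 or 15 points could be taken as a reason to adopt the app in the definitive trial, or a small gap as evidence that the two methods are equivalent, when the data could support neither conclusion. The trial's main feasibility outcomes are not affected.

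**Working it through.** **Stated purpose against stated analysis**

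| Place in the protocol article | What it commits to |
|---|---|
| Objectives, number 7; Table 3 | Whether adherence differs, app v diary |
| Randomisation and concealed allocation | 1:1 allocation, 16 v 16 |
| Study Within A trial (SWAT) | Allocation made in order to test objective 7 |
| Statistical analysis | Percentages for the EDX group; no contrast, no interval for a contrast |

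The first three rows describe a two-group comparison. The fourth does not complete it. The article gives no adherence figure, so there is no number of its own to reproduce.

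**Precision of the missing contrast**

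Inputs: n = 16 per group (from the protocol article). The SD of participant-level adherence is not given, so 25 percentage points is assumed, with a range of 20 to 30.

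Formula: half-width = t(30 df, 0.975) × SD × √(2/16), where t = 2.042 and √(2/16) = 0.3536.

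- SD 20: 2.042 × 20 × 0.3536 = 14.4 points
- SD 25: 2.042 × 25 × 0.3536 = 18.1 points
- SD 30: 2.042 × 30 × 0.3536 = 21.7 points

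These figures assume that all 32 participants supply adherence records; missing records would widen them. They also assume that a t interval on participant-level percentages is a fair approximation. On the central assumption, an observed difference of 15 points would have an interval from about −3 to +33.

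**Does the frequency wording distort the comparison?**

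Over eight weeks, a literally daily programme gives 7 × 8 = 56 days, and six days a week gives 6 × 8 = 48. If the same denominator is used in both arms, changing it rescales both by 48/56 = 0.857. A 20-point difference would read as 20 × 0.857 = 17.1 points, and the app/diary ratio would not change. The level of adherence moves, but this choice does not by itself bias app against diary.

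**The case against.** The strongest reply is that this is a condensed article on a feasibility trial. The comparison is stated in the objectives, in Table 3 and in the SWAT section. The analysis clause says that adherence is reported within the SWAT, which may well mean by arm. The section opens by saying that descriptive analysis will include proportions with 95% intervals. Describing 16 v 16 without a formal test is reasonable, and details of the contrast could sit in an analysis plan that is not shown.

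Much of this stands. No hypothesis test is needed, and reporting by arm is a fair reading. But two percentages, even each with its own interval, do not give the difference or its interval. The point also does not rest on silence alone: the clause states what form the reporting will take, and that form falls short of the stated objective, while intervals are named for recruitment and retention in the same paragraph.

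A reader might go further and infer that the adherence percentage has conflicting denominators: daily, six days a week, or six days a week in weeks 3 to 8 only. On that view a fully adherent participant could score 48/56 = 86%. The document does not support this.

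- The Interventions section gives six days a week without limiting it to particular weeks, and its later statement for weeks 3 to 8 agrees. For the first week it says "Week 1 will focus on familiarisation with the basic program and load management strategies", which describes content and sets no different frequency; week 2 is treated in the same way. There is no third basis.
- The daily wording occurs in the Background and is never tied to the adherence calculation. The 86% would arise only if an analyst counted a stated rest day as exercise due, and nothing tells them to.
- The article gives no adherence denominator at all, and that detail can properly be left to the full protocol or analysis plan.
- Shifts in the level of adherence caused by a change of denominator should not be set against the half-width for a between-arm difference. They are different quantities.

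**Conclusion.** The point holds as a mismatch between objective and analysis. Objective 7 and the second randomisation call for a comparison of app with diary, and the stated reporting does not deliver an estimate of it. The interval that should accompany the difference has a half-width of about 18 points if the SD is 25, and about 14 to 22 points for SDs of 20 to 30. The SDs are assumptions, and complete records from 16 per group are also assumed. The SWAT can therefore give a rough estimate for planning but cannot settle the question, and the report should show this.

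The difference between the Background's daily programme and the six days with a rest day in the Interventions section is a real but minor inconsistency of wording. The two should be reconciled; no view is taken here on which is right.

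**What to change.** In the Statistical analysis section, replace the adherence clause with a statement to this effect: adherence will be summarised for each SWAT arm, with participants analysed as randomised; the app-minus-diary difference will be reported with its 95% confidence interval; and this will be presented as an estimate to inform the definitive trial, not as a powered test.

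Add that adherence is computed identically from app and diary records, relative to what each participant was prescribed. The number of exercises varies from four to six and programmes are modified individually, so this puts participants on a common footing. Therapists are given access to Physitrack for prescribing, and both SWAT groups use its companion app for their exercises, so the prescriptions should be retrievable in both arms.

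Separately, reconcile the frequency wording between the Background and Interventions sections.

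The cost is a few lines of text and a little extra data handling. Design, sample size and data collection do not change.
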